### MBI and psychological well-being

Besides the theoretical functions of mindfulness, scholars also examined the clinical effectiveness of mindfulness practice in reducing parents’ psychological distress. Existing research has provided evidence that mindfulness practice is effective in reducing stress and enhancing psychological well-being in a variety of clinical and non-clinical groups, particularly with individuals under chronic stress conditions, such as chronic disease, burnout, and caring for individuals with chronic conditions [29–31]. Mindfulness-based practice is also found to be associated with neural changes in specific brain regions, with subsequent effects on attention, affective regulation, mood, psychological well-being, and behavior [32, 33].

Adding mindfulness-based components to existing behavioral knowledge resulted in measurable positive changes and reduced parental stress for parents of children with developmental disabilities [34]. There was also specific clinical evidence showing the effectiveness of MBI on parents of children with ASD. The effect size of a mindfulness intervention on the subjective well-being of caregivers of children with ASD was 0.79 in single-group design (p < 0.01) and 0.43 in randomized control trials (p < 0.001) [35].

### Ecological momentary intervention and assessment (EMI/A)

There are three main research gaps in understanding the mechanisms of psychological distress in parents of children with ASD and the effectiveness of using MBI for reducing psychological distress. First, due to significant recall bias, traditional observational studies cannot accurately quantify the relationship between life events, cognitive appraisal, and psychological distress. Second, the moderating effects of MBI on modifying parents’ cognitive appraisal and psychological distress have not yet been explored with a robust methodology. Third, the traditional delivery face-to-face mode of mindfulness, was hard to attract a large population of parents of children with ASD as these parents are already occupied by their duties of parenting children and maintaining the function of the whole family. Therefore, a newly developed ecological momentary intervention (EMI) and assessment (EMA) platform to deliver MBI is worth exploring.

Patrick et al. first raised the term “ecological momentary intervention” in 2005 [36], which was later defined as “treatments that are provided to people during their everyday lives (i.e., in real-time) and in natural settings (i.e., real-world)” [37]. Normally, using EMI means delivering treatment on mobile phones and being implemented standalone or as a supplement to existing treatments. Meanwhile, EMA is defined as a method using wearable electronic devices to repeatedly document and collect human thoughts, emotions, behavior, and physiological states in the natural environment context [38]. As a special observational study technique, EMA can minimize recall bias, maximize ecological validity, help understand the dynamic interplay between events of interest, and enable ecological momentary interventions [39].

There are several benefits of using EMI and EMA. First, the application of EMI enables researchers to reach large populations easily, rapidly, and cheaply [40]. Secondly, using EMI can modify the contents of intervention based on individual and contextual factors that vary across time and to fit individual needs and backgrounds. Thirdly, By using EMI, participants can practice the skills and exercises in real-life settings that fit their day-to-day routine, reducing the burden on parents of children with ASD to change their daily schedule [40]. Lastly, using EMA enables researchers to obtain information with maximized ecological validity and to track behaviors and experiences change over different periods and contexts [41].

Existing research has offered clinical evidence supporting the effects of EMI and EMA in promoting healthy behavior and psychological well-being [40, 42]. Yet, the literature search on PubMed found no prior study examined the effects of MBI using EMI for parents of children with ASD. Only one study protocol was proposed to explore mindfulness intervention and EMI to decrease adolescent stress and anxiety [43]. The knowledge in filling the above research gaps is essential for examining the mechanism between life events, cognitive appraisal, psychological distress, and methods for reducing the psychological distress of parents of children with ASD.

This study aims to develop and implement the MBI using EMI and EMA platform (EMI/A-MBI) and to assess the effectiveness of this newly developed EMI/A-MBI on reducing psychological distress in parents of children with ASD. Specifically, we aim:

to identify the daily sources of depression, anxiety, and stress in parents of children with ASD and what are the protective factors for resilience;(comparison of the intervention and control group) to evaluate the effectiveness of EMI-MBI in improving the psychological well-being of parents of children with ASD;(within the intervention group) to explore whether the intensity and frequency of mindfulness practice moderate the participants’ cognitive appraisal of daily life events and their psychological distress and mental well-being.

### Research hypotheses

The research hypotheses of this proposed study include the following:

The intervention group would show a significant reduction in depression, anxiety, and stress than the control group right after intervention and during follow-up.The intervention group would significantly increase life satisfaction and empowerment more than the control group right after intervention and during follow-up.The intensity and frequency of mindfulness practice would moderate the relationship between participants’ cognitive appraisal of daily life events and psychological distress and mental well-being in the intervention group.

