#### Sample size

The sample size calculation for this study is based on the linear mixed model that will be adopted to answer research questions 1 and 2 based on the repeated ecological momentary assessment data from the intervention and control group and the effect size of 0.29 from previous studies (unpublished manuscript). The R package *sjstas* [44], and *pwr* [45] were used for sample size calculation. The results indicate that a total of 536 participants will be required to detect a significant difference at an alpha level of 0.05 and a power of 80%. Accounting for potential dropouts, we conservatively estimate that 20% of participants may not complete the study. Therefore, we plan to recruit 670 participants (335 in each group).

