#### Outcomes

At baseline, post-test, and follow-up survey, the questionnaire contains the same questions concerning demographic information (will only ask at baseline). Psychological distress and mental well-being will be administered to participants in both intervention and control groups. Demographic information, including parent and children’s gender, parent and children’s age, years of children diagnosed with ASD, number of children living in the same household, family monthly income, parents’ education level, parents’ employment status, and average time spent with children daily. The primary outcome will be participants’ psychological distress measured by the depression anxiety stress scale. The secondary outcomes will include participants’ subjective well-being, measured by the satisfaction with life scale, and level of resilience, measured by the psychological empowerment scale. (Detailed measurement information can be found in Fig 3)

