**Fig 3 pone.0291168.g003:**
[figure not shown]
Summarizations of measurements.

*The cognitive Appraisal of Health Scale* will be used to measure participants’ cognitive appraisal of daily life events. This scale includes 28 items rated from 1 strongly disagree to 5 strongly agree. This scale was developed based on the transactional theory of stress and coping and thus consists of subscales of primary appraisal (threat, challenge, harm/loss, and benign/irrelevant) and secondary appraisal. The internal consistencies were all greater than 0.70 [46].

*The Five Facet Mindfulness Questionnaire (FFMQ)-short version* [47, 48] will be used to measure participants’ level of mindfulness before and after practicing. It includes 15 items measuring the five facets of mindfulness: observing, describing, acting with awareness, non-judging of inner experience, and non-reactivity to inner experience. This scale was further validated [49] and yielded good convergent validity and internal consistency [49].

Parents’ psychological distress will be assessed in the domains of depression, anxiety, stress, and mental well-being, indicating participants’ life satisfaction and empowerment.

*The Depression Anxiety Stress Scale (DASS)* [50] is a self-report questionnaire that measures the emotional states of depression, anxiety, and stress. This scale contains 21 questions rated from 0 (did not apply to me at all) to 3 (applied to me very much, or most of the time). There were seven questions for each sub-scale of stress, depression, and anxiety [51]. This scale was reliable (alpha = 0.96 and 0.80 for the depression and anxiety subscales, respectively). Cronbach’s alpha was high for the three subscales in parents of children with ASD: 0.91 for stress, 0.87 for anxiety, 0.94 for depression, and 0.92 for full scale [51]. It has also been validated in the Hong Kong population [52].

*Satisfaction with Life Scale (SWLS)* [53]. The SWLS has five items scored on a 7-point scale (1 = strongly disagree to 7 = strongly agree) measuring participants’ satisfaction with life and has a Cronbach’s alpha for internal consistency of 0.87 and a test-retest correlation of 0.82 [53]. This scale has also been validated in Chinese [54] and Hong Kong populations [55].

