### Data analysis

Data analysis will be conducted using STATA 17 [60]. All significance tests were two-sided with a 5% level of significance. Missing data will be calculated using intention-to-treat approach. Participants who failed to answer the prompted questions will be treat as no improvement on the outcomes. The characteristics of the observed data and the missing data will be compared to determine whether there are any systematic differences. If tested that the missing data will be missing not at random, imputation methods, such as multiple imputation (MI) or maximum likelihood estimation (MLE), will be adopted to estimate the missing values based on the observed data and the relationships between variables. Moreover, sensitivity analysis will be adopted to assess the impact of the missing data on the study results and to determine the robustness of the findings. Complete case analysis and multiple imputation will also be conducted as sensitivity analysis. The internal consistency of the constructs for mindfulness, depression, anxiety, stress, and life satisfaction will be assessed with Cronbach’s alpha. In each construct, the PI will sum all items to build the score for that attribute in each participant.

To answer the first and second questions, first of all, the effect size (Heges’ g) of the outcome for both the intervention and control groups will be calculated. Subgroup analysis will be conducted when necessary. Next, linear mixed models will be conducted to compare the effectiveness of the mindfulness intervention between the two treatment groups. Linear mixed models are particularly suitable for analyzing data collected via ecological momentary assessment, as they can account for the nested and repeated nature of the data. The main predictor variable will be the treatment group (intervention vs. control), and the model will also include baseline DASS scores and any relevant demographic variables (e.g., age, gender) as covariates. The linear mixed model will include random intercepts and slopes for each participant to account for individual differences in the baseline scores and the rate of change in scores over time. The treatment group effect will be assessed using a fixed effect, and the model will also include an interaction term between treatment group and time to investigate any differential effects of the intervention over time.

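### Hypothesis 1 covers up to six comparisons at an unadjusted two-sided 5%, and the protocol names no primary score, time point, model term or success rule

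*Protocol article*

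**What the plan says.** - **Research hypotheses.** The first hypothesis is that the intervention group will "show a significant reduction in depression, anxiety, and stress than the control group right after intervention and during follow-up".
- **Outcomes.** The primary outcome is "participants’ psychological distress measured by the depression anxiety stress scale". Neither this section nor the abstract says whether that means the total or a subscale, or which assessment is primary.
- **Measurement descriptions (with Fig 3).** "There were seven questions for each sub-scale of stress, depression, and anxiety". Reliability is cited for each subscale and for the total ("0.94 for depression, and 0.92 for full scale"), so a single score is available.
- **Data analysis.** "All significance tests were two-sided with a 5% level of significance". On scoring: "The internal consistency of the constructs for mindfulness, depression, anxiety, stress, and life satisfaction will be assessed with Cronbach’s alpha". One sum score is then built per construct. Depression, anxiety and stress appear as separate constructs, and a DASS total does not appear. The linear mixed model has a fixed group effect and a group-by-time interaction, and neither is named as the primary test.
- **Sample size.** The calculation gives 536 participants to "detect a significant difference at an alpha level of 0.05 and a power of 80" per cent, raised to 670 for 20% dropout. It is framed as a single comparison.

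**The concern.** The choice of one primary comparison belongs in a protocol. Here the hypothesis, the outcome definition and the analysis each leave it open, while the test level is fixed at 5% throughout. Up to six results could each be presented as the primary effect, and which one leads could be settled after the data are seen. The error rate of 0.05 used to size the trial describes one test, and Hypothesis 1 as worded is not one test.

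**Working it through.** **Inputs from the protocol.** Three subscales and two post-baseline survey times, so 3 × 2 = 6 comparisons if each is tested separately. Level: two-sided 5% per test, hence 2.5% per test in the direction of benefit. Sizing: alpha 0.05, power 80%, effect size 0.29, 536 before dropout, no interim analysis.

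**Assumed inputs.** The correlations between test statistics are not given. I take 0 to 0.8 between subscales and 0 to 0.7 between times, as a product structure.

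**The plan's own figure.** 536 / 0.80 = 670, so the dropout step reproduces. A plain two-sample comparison at d = 0.29, two-sided 5% and 80% power needs 374 to 376 in total. The planned 536 would correspond to a factor of about 536 / 375 = 1.43. The sample size is said to rest on a mixed model whose inputs are not reported, so this does not show 536 to be wrong. What matters here is that the calculation uses one alpha of 0.05 and one effect.

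**Reading A: six tests, any one counts as success, no true effects.** For independent tests the formula is 1 − (1 − α)^6. For correlated tests the figures come from simulating 1,000,000 draws of six correlated normal test statistics.

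| Correlation (subscales / times) | Any false significant difference, either direction | False result favouring the intervention |
|---|---|---|
| 0 / 0 | 1 − 0.95^6 = 26.5% | 1 − 0.975^6 = 14.1% |
| 0.5 / 0.5 | 22.0% | 11.1% |
| 0.8 / 0.7 | 15.9% | 7.9% |
| One test, for comparison | 5% | 2.5% |

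**Reading B: DASS total at two times, either counts.**
- Independent: 1 − 0.95^2 = 9.8% in either direction and 1 − 0.975^2 = 4.9% for benefit.
- Time correlation 0.7: 8.4% and 4.2%.

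**Reading C: all six must be significant.** A claim then needs every true null to be rejected in the direction of benefit, so the false-benefit rate cannot exceed 2.5%. With no true effect anywhere it is below 0.2%. The cost is power. If each test had 80% power, the chance that all six succeed is 0.8^6 = 26% when independent and about 57% by simulation at correlations 0.8 / 0.7.

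The single-test alpha and power in the sample size section therefore fit Hypothesis 1 under none of these readings: A and B exceed the stated alpha, and C falls short of the stated power.

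**The case against.** Four counter-arguments deserve weight.

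1. **Six is not fixed.** One instrument is named as primary, a full-scale reliability is cited, and the analysis is a repeated-measures model rather than separate tests at each visit. This stands: six is the upper reading. It is still a plausible one, because the scoring paragraph lists the three domains separately and no total.
2. **The hypothesis joins its parts with and.** Read literally, every part must be shown, and then nothing is inflated. That is correct as logic, but no such decision rule is written, and the sample size is not built for it.
3. **The article is condensed.** The measurement figure and the full protocol are not visible, and a multiplicity procedure is commonly left to an analysis plan. This is fair for the procedure itself. It does not remove the conflict between the visible statements: an open-ended primary hypothesis, a primary outcome without score or time point, and 5% for all tests.
4. **The size can be overstated.** A reader might infer that the risk of falsely claiming benefit is 16-26% instead of 5%. The documents do not support that. The tests are two-sided, so 16-26% counts false differences in both directions. For benefit alone the figures are about 8-14% against 2.5%, and only if any one result is enough.

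**Conclusion.** The point holds in a limited form. Hypothesis 1 allows up to six comparisons, and the protocol fixes no primary score, time point, model term or success rule while setting each test at two-sided 5%. If any one significant result counts as success, the error rate is roughly three to six times nominal for a false claim of benefit (8-14% against 2.5%) and three to five times for any false difference (16-26% against 5%). With a DASS total at two times it is a little under double on either count. These sizes depend on the assumed correlations and on the any-one rule, which the protocol neither states nor excludes. It would be wrong to read the protocol as committed to six tests or to that rule. The defect is that it commits to no rule at all. It should be corrected.

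**What to change.** Before any data are seen, name one primary comparison and use the same wording in the hypotheses, outcomes, sample size and analysis sections. One workable version:

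- **Primary:** the group contrast in DASS-21 total at the 8-week post-test, from the linear mixed model, at two-sided 5%. State which model term gives it, for example the group-by-time term at that visit, and that it uses the survey scores rather than the daily app assessments.
- **Next in order:** the 2-month contrast in the total, tested only if the first is significant.
- **Secondary:** depression, anxiety and stress subscales, either Holm-adjusted or as estimates with confidence intervals.

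Two alternatives would close the gap equally well: keep several primary comparisons under a stated multiplicity procedure, or require all of them to be significant. In either case, restate the power to match.

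The recommended version costs wording only and needs no extra data. Its downside is that the subscale results lose primary status. The alternatives keep that status but may need a larger sample or an acceptance of lower power.

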## Methods

### Trial design

This research adopts a parallel-armed, randomized controlled trial (RCT) design. The intervention group will receive a combination of (1) a time-based system-triggered EMA, which will collect participants’ sources and status of depression, anxiety, and depression in daily life; (2) EMI-delivered MBI, and (3) a follow-up survey of long-term effects of EMI/A-MBI. The participants will complete a baseline questionnaire and then participate in EMI via a smartphone application (App) for eight consecutive weeks and receive the daily exercise prompts. The EMA will include questions about self-reported depression, anxiety, and depression. After the 8-week EMI/A-MBI, the participants will be invited to complete a post-experimental survey with similar questions in the baseline questionnaire. Two months after completing the EMI/A-MBI, participants will be contacted to complete a telephone follow-up survey with similar questions in the baseline questionnaire. The control group will receive the longitudinal survey exactly the same as the intervention group and 8-week mindfulness-based short messages sent by the research team on a daily basis. The messages will contain audio-based instructions for mindfulness-based practice, which will be the same as the intervention group. The SPIRIT schedule of enrolment, interventions, and assessments can be found in Fig 1 and the flowchart of the design can be found in Fig 2. (The SPIRIT checklist can be found in S1 File).

**Fig 1 pone.0291168.g001:**
[figure not shown]
SPIRIT schedule of enrolment, intervention and assessment.

**Fig 2 pone.0291168.g002:**
[figure not shown]
Flowchart of participants through the trial.

#### Study setting

This study will be conducted in Hong Kong and recruit parents of children with ASD from local organizations for ASD, such as Autism Hong Kong, Autism Partnership Foundation, or Autismilee. The study sites will be the current living environment of the participants for the participants’ convenience.

#### Participants

The inclusion criteria will comprise (1) parents of children with ASD (children aged between 6–18 and diagnosed with different functional levels of ASD by certified psychologists); (2) own a mobile smartphone with internet access; (3) will stay in Hong Kong during the 8-week EMI/A-MBI study period, and (4) able to read and write in Chinese. The exclusion criteria will include (1) parents diagnosed with depression, anxiety, and stress disorder by certified doctors; and (2) parents who do not live together with their children with ASD on a daily basis.

After participants enrol online or are recruited offline from community centers, the research assistant (RA) will explain the study objectives and procedure to participants and get informed consent from all participants.

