#### Randomization and allocation

Individual randomization by a serially numbered opaque sealed envelope (SNOSE) will be used to ensure the allocation sequence was concealed from research assistants and participants before the group allocation. The principal investigator (PI) will prepare about 200 identical, opaque, sealed A5-sized envelopes, with a unique three-digit serial number on the cover of each envelope as an identifier. Half of the envelopes contain an action plan for the intervention group, and the remaining half contains an action plan for the control group. After inserting the intervention materials in the envelopes, they will be sealed, shuffled, and then numbered. When the participant consents to participate, the research assistant opens one envelope according to the serial number sequence and assigns the participant to a treatment condition based on the action plan. All the participants will not be blinded to the given interventions. Outcome assessors (research assistants) are blinded to the group allocation at the telephone follow-up.

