To answer the third question, structural equational modelling will be adopted to examine the pathways of the relationship between daily life events, cognitive appraisal, and psychological distress. Moderation analysis will also be used to explore the effects of mindfulness. The model will be adjusted for the participants’ role of mother or father. Bootstrapping with size 10,000 will be used to estimate the 95% confidence interval of the parameters. After checking data distribution normality, several fit indices will be served as the judgment of the fit of the model. A non-significant chi-square (X^2^) is desired, but the test is sensitive to erroneously reject a correct model when the sample size is not large enough [61]. The Comparative Fit Index (CFI) and the Non-Normal Fit Index (also known as the Tucker-Lewis Index, TLI), ranging from 0.00 to 1.00, with higher values representing better fit, will be adopted [62]. The standardized root-mean-square residual (SRMR) and root mean square error of approximation (RMSEA) will be used to detect model misspecifications, with values below 0.08 considered desirable [62]. The indirect effect of the model will be checked with the Sobel test.

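### Both parents sharing a home with the child may enrol and are randomised separately, so about half of any enrolled couples would be split between arms, which could dilute the app-versus-audio contrast

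*Protocol article*

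**What the plan says.** Under Participants, the first inclusion criterion covers "parents of children with ASD (children aged between 6–18 and diagnosed with different functional levels of ASD by certified psychologists". The unit is the parent, and no criterion refers to a second parent of the same child. One of the two exclusions removes "parents who do not live together with their children with ASD on a daily basis".

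Under Randomization and allocation, "Individual randomization by a serially numbered opaque sealed envelope (SNOSE) will be used". The allocation is 1:1: "Half of the envelopes contain an action plan for the intervention group, and the remaining half contains an action plan for the control group". On consent, the next envelope in serial order is opened. No rule covers a participant whose spouse is already in the trial.

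Under Data analysis, the comparison of arms uses a mixed model: "The linear mixed model will include random intercepts and slopes for each participant". No family level is named. For the third research question, "The model will be adjusted for the participants’ role of mother or father", so both mothers and fathers are expected.

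The section explaining the choice of comparators says that both arms receive mindfulness content and that any additional benefit in the intervention arm is to be credited to EMI and EMA.

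**The concern.** Read together, these rules let both parents of one child enrol and then randomise them independently. Some control parents would live with a partner who has the app, its chatbot and its exercise library. Study setting names the participants' own living environment as the study site, so a split couple shares that site.

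The benefit could reach the control parent in two ways. One is direct: the partner's exercise library holds audio, video and scripts that are easy to share. The other needs no sharing. The Introduction says that parental distress may worsen children's behaviour, that problem behaviour is a source of parental stress, and that family support eases distress. A parent who improves could therefore lower the spouse's score on the primary outcome.

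Either route moves the control mean toward the intervention mean. The contrast already sets the app against an active comparator, so the bias is toward a false null.

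Two safeguards in the text do not reach this case. The concomitant-care section asks participants to avoid mindfulness practice from outside the study, and a spouse's study app is not clearly outside it. The limitation in the Discussion concerns controls who seek other services, not exposure through another participant.

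**Working it through.** **Plan's own figures.** Sample size states an effect of 0.29, 80% power, alpha 0.05, 536 participants before dropout and 670 after 20% dropout. Data analysis states two-sided tests.
- 536/0.8 = 670, which reproduces.
- A plain two-sample comparison at d = 0.29 needs 187 per arm (374) by the normal formula, or 188 per arm (376) by the t-test. Reaching 536 needs a design effect of about 536/375 = 1.43, whose inputs are not printed. That is a separate matter. Below, 536 is taken as giving 80% power.

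**How many couples are split.** With 335 places per arm, once one parent is placed, 335 of the remaining 669 places are in the other arm: 335/669 = 50.1%. Within one set of 200 envelopes it is 100/199 = 50.3%.

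**Dilution.** Let f be the share of participants enrolled as couples and c the share of the app's added effect that reaches a control parent with an app-using partner. Neither is in the documents; both are assumptions. Of N participants there are fN/2 couples, and half of them (fN/4) are split, each contributing one control. As a share of the N/2 controls this is f/2. The control mean shifts by c × d × f/2, so

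d observed = 0.29 × (1 − c·f/2).

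Write a = 1 − c·f/2. Power is Φ((1.960 + 0.842)·a − 1.960), and the number of completers that restores 80% power is 536/a².

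| f | c | a | d | Power | Completers needed | With 20% dropout |
|---|---|---|---|---|---|---|
| 5% | 25% | 0.99375 | 0.288 | 79.5% | 543 | 679 |
| 10% | 50% | 0.975 | 0.283 | 78% | 564 | 705 |
| 20% | 50% | 0.95 | 0.276 | 76% | 594 | 743 |
| 40% | 50% | 0.90 | 0.261 | 71% | 662 | 828 |
| 40% | 100% | 0.80 | 0.232 | 61% | 838 | 1048 |

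**Spousal correlation.** Under individual 1:1 allocation, couples in the same arm inflate the variance of the difference and split couples deflate it by nearly the same amount. A simulation of a simple comparison of means (N = 536, 20,000 runs, no effect, Monte Carlo error about 0.15 points) gave these type I errors with the correlation ignored:
- no couples: 5.0%
- f = 40%, ρ = 0.3: 4.9%
- f = 100%, ρ = 0.3: 5.2%
- f = 100%, ρ = 0.6: 5.1%

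The test stays essentially at its nominal level.

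**The case against.** The strongest reply is that the point rests on what a condensed article does not say. The approved protocol is a supplement that is not shown, and a one-per-household rule could stand there. This stands only in part. The article does state the eligibility criteria, the unit of randomisation and the random-effects structure, and together they permit split couples. Contamination is also not something an analysis plan can undo after allocation.

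The second reply is that nothing shows couples will enrol. This stands. Adjusting for parental role shows that mothers and fathers are expected, not that both parents of one child are, and Recruitment addresses individual volunteers. The range must therefore start near zero.

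The third reply is that full carry-over is implausible. Controls already have mindfulness audio, and much of what the app adds is tied to its user: check-ins three times a day, self-ratings that drive recommendations, a personal emotion log and adherence reminders. This also stands, so c = 100% is an upper bound.

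A reader might infer two stronger claims that the documents do not support. One is that a split couple necessarily passes the app to the control arm; sharing is possible, but nothing in the text establishes it. The other is that the missing family term invalidates the test; under individual 1:1 allocation, the simulation shows almost no effect on type I error.

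**Conclusion.** The point holds as a design weakness of uncertain size. Followed as written, the protocol would place about half of any enrolled couples in opposite arms within one home, with a possible bias toward zero in the trial's main contrast. The effect falls from 0.29 to between 0.288 and 0.232 over f = 5–40% and c = 25–100%, with about 0.276 at f = 20%, c = 50%. If 536 gives exactly 80% power, the matching power runs from 79.5% to 61%.

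These figures depend on f and c, which the documents do not give. If few couples enrol, the loss is trivial. If the unexplained design effect behind 536 were unnecessary, 268 per arm would give about 92% power at 0.29, which leaves some room for dilution. The harm is contamination, not the unmodelled spousal correlation. The change is worth making because it is simple before enrolment and unavailable afterwards.

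**What to change.** Before enrolment starts, adopt one of two rules.

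1. Add to eligibility that one parent per family may take part, chosen before randomisation. This removes within-couple contamination. It loses about f/2 of participants: 2.5% (about 17 of 670) at f = 5%, 10% (67) at f = 20% and 20% (134) at f = 40%. These should be replaced from other families within the planned six-month recruitment. If they are not, precision falls by a factor of √(1 − f/2), which at f = 20% is 0.949. That is about the same power cost as dilution at c = 50% (0.95), so the gain would then be in bias and not in power.

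2. Allow both parents, allocate the family with a single envelope, and add a family random intercept to the linear mixed model. No participants are lost, but the family term now matters, because both spouses are always in the same arm. The design effect is roughly (1 − f) + f(1 + ρ) = 1 + f·ρ. With ρ = 0.3 as an assumption, it is 1.015 at f = 5%, 1.06 at f = 20% and 1.12 at f = 40%. The last raises 536 completers to 601, against 838 under full dilution at the same f. At f = 5% it raises 536 to 545, against 543 for mild dilution (c = 25%), so there the benefit is again lower bias.

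The first rule is one sentence in the eligibility criteria. The second needs a sentence on allocation, a family identifier in the data and one more variance term.
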